## Abstract

**Background**: Attention-deficit/hyperactivity disorder (ADHD) often persists into adulthood, causing substantial functional impairments. While pharmacological treatments are considered first-line, many adults either decline or do not benefit from medication, underscoring the need for effective non-pharmacological interventions. **Objective**: This study describes the protocol for a randomized controlled trial (RCT) evaluating Sincrolab Adults, an AI-based cognitive stimulation program for adults with ADHD. The primary objective is to determine whether 12 weeks of intervention improves cognitive performance. Secondary and exploratory objectives assess its impact on ADHD symptoms, quality of life, and durability of effect. **Methods**: The study will employ a single-blind, multicenter, randomized controlled design comparing the digital cognitive intervention to a treatment-as-usual control group. A total of 104 adults diagnosed with ADHD will be randomized to either the Sincrolab Adults program or the control group. Outcomes will be measured using the MOXO Continuous Performance Test (CPT) for cognitive performance, the Adult ADHD Self-Report Scale (ASRS) for symptoms, and the Adult ADHD Quality of Life (AAQoL) scale. A one-month post-intervention follow-up will assess persistence of effects. **Results**: The primary outcome will be improvement in the CPT total score. Secondary outcomes include reductions in the ASRS symptoms. Exploratory outcomes will examine quality of life, ADHD symptom subdomains, and durability of improvements. **Conclusions**: This study will provide evidence on the feasibility and preliminary efficacy of a digital cognitive stimulation platform for adults with ADHD. Findings could support the development of scalable, accessible treatment alternatives for individuals with ADHD.

## 1. Introduction

Attention-deficit/hyperactivity disorder (ADHD) is among the most common childhood psychiatric disorders affecting 2.6–4.5% of children worldwide [1] and often persists into adulthood, with prevalence rates of 2–5% [2,3,4].

Adults with ADHD often experience significant psychosocial and functional challenges, including elevated levels of perceived stress [5], diminished academic and occupational productivity [6], and a greater likelihood of involvement in criminal behavior [7]. ADHD in adulthood also generates substantial healthcare costs [8]. A systematic review estimated that 89.5% of the global economic burden of ADHD falls on adults, while only 10.5% is attributed to children and adolescents [9]. In Spain, the average annual cost per adult is EUR 15,652, with an additional one-time cost of EUR 7893. These costs are primarily driven by economic factors (50%), social consequences (28%), healthcare spending (52%), and legal issues (42%) [10].

Pharmacological treatments, particularly stimulants, are considered first-line interventions for adults with ADHD [11] and have demonstrated efficacy in reducing core symptoms [12,13]. However, their impact on higher-order cognitive functions, such as executive functioning, working memory, or planning, remains limited, with many of these deficits persisting despite symptom improvement [14,15]. Moreover, these medications are frequently associated with side effects, including decreased appetite, abdominal pain, headache, irritability, insomnia, and increased anxiety. In rare cases, more serious psychiatric reactions such as mood disturbances or suicidal ideations have been reported, particularly in vulnerable individuals [16]. Consequently, many young adults discontinue medication to avoid dependence and adverse effects [17]. These limitations have contributed to increasing interest in non-pharmacological approaches, such as psychotherapy, psychosocial interventions, coaching, and skills training, as complementary or alternative approaches for managing ADHD in adults [18]. Guidelines from both the European Network Adult ADHD and the UK’s NICE recommend the use of psychological interventions, particularly cognitive behavioral therapy [19,20]. Cognitive training, a potentially valuable rehabilitation approach, has been minimally explored for adults with ADHD. Existing studies yield inconsistent results, possibly due to methodological variations or limitations. These interventions have demonstrated only modest improvements in cognitive performance in adults with ADHD, and evidence supporting their effect on core ADHD symptoms remains limited [21,22,23]. A recent meta-analysis found low-quality evidence for improvements in symptom severity, including reductions in inattention and hyperactivity/impulsivity. Additionally, the meta-analysis also highlighted the potential of digital interventions to enhance monitoring and patient–provider communication [24].

Neuroimaging studies implicate functional connectivity dysfunctions and neurocognitive deficits in cortical regions underlying impairment among individuals with ADHD [25]. These deficits manifest as deficits in sustained, selective, and divided attention [26], as well as in tasks related to executive functions, particularly inhibitory control, working memory, decision-making, and planning [27]. Additionally, deficits in processing speed and response time consistency have been observed [28]. Despite the promise of non-pharmacological treatments, their effects on cognitive rehabilitation remain limited [2,29].

Sincrolab Kids and Sincrolab Adults are innovative cognitive stimulation tools developed through collaboration among neuropsychologists, programmers, and video game designers. These tools employ gamified tasks grounded in neurorehabilitation principles and leverage the motivational and engaging aspects of video games. By immersing users in virtual environments that require integrated cognitive processing, these tools aim to promote the transfer of cognitive training to everyday tasks.

An artificial intelligence engine embedded in both tools dynamically adjusts task difficulty to maintain a performance level near 50%, ensuring individualized training programs tailored to each user’s abilities. Sincrolab Kids has undergone initial validation in a neurotypical population of 40 children aged 8–12, demonstrating significant improvements in inhibitory control and processing speed. A subsequent clinical trial with children diagnosed with ADHD-C incorporated behavioral assessments and neurophysiological measures via magnetoencephalography. Preliminary findings demonstrated significant improvements in visuospatial and phonological working memory, processing speed, and verbal fluency, along with enhanced functional connectivity between cortical regions [30,31,32], consistent with known neurocognitive correlates of ADHD [25].

Validation of cognitive stimulation tools like Sincrolab should follow an iterative and systematic process, tailored to the specific needs of different populations such as adults versus children with ADHD, individuals with varying symptom profiles, or those with other clinical conditions, including mild cognitive impairment [33]. Building on the successful validation of Sincrolab Kids for children and adolescents with ADHD, there is an urgent need to address the scarcity of scientifically validated non-pharmacological treatments for adults with ADHD. To this end, a randomized, single-blind, multicenter clinical trial is planned to evaluate the efficacy of Sincrolab Adults to expand therapeutic options for this underserved population.

## 2. Study Objectives

### 2.1. Primary Objective

The primary aim of the present study is to assess the efficacy of Sincrolab Adults in improving cognitive–functional performance in adults diagnosed with ADHD (any presentation) who are either not receiving pharmacological treatment or for whom medication has proven ineffective. The study aims to demonstrate that participants undergoing training with Sincrolab Adults exhibit significant improvements compared to those receiving a treatment-as-usual (control group). These improvements will be assessed using the MOXO Continuous Performance Test total score [34].

### 2.2. Secondary Objectives

The secondary aim is to assess whether treatment with Sincrolab Adults, compared to the control group, leads to significant changes in functional ADHD symptoms as measured using the Adult ADHD self-report Symptom Rating Scale (ASRS) [35]. Additionally, the study aims to evaluate whether these improvements reach clinically significant levels, defined as a minimum change of 12 points between baseline and post-treatment scores [36].

### 2.3. Exploratory Objectives

The exploratory aim is to (1) evaluate whether treatment with Sincrolab Adults, compared to the control, leads to significant improvements in quality of life, as measured with the Adult ADHD Quality of Life Questionnaire (AAQoL) [37]; (2) assess whether treatment with Sincrolab, compared to a control group, leads to significant improvements in the remaining indices from MOXO (attentiveness, timing, impulsivity, and hyper-reactivity); (3) to examine potential correlations between cognitive and functional outcomes—specifically, the study will investigate the relationship between CPT performance indices and functional symptoms and quality of life related to ADHD; and (4) to assess the durability of the effect of Sincrolab Adults following 1 month without intervention.

By addressing these objectives, this study aims to provide preliminary evidence for the feasibility and efficacy of Sincrolab Adults as a non-pharmacological intervention for adult ADHD, potentially offering a novel therapeutic approach for individuals who do not respond adequately to medication.

## 3. Materials and Methods

### 3.1. Design and Participants

This study is a parallel, randomized controlled trial (RCT) with a treatment-as-usual control group, employing a single-blind design to minimize bias. (Outcome assessors will be blinded to group allocation).

This study will include 104 adults aged 18 and older to evaluate Sincrolab Adults (v.4.0.24) (60% male/40% female, reflecting ADHD prevalence in Spain). The study will consist of adults with ADHD, with any presentation, who are stable on or off medication doses (for at least 2 weeks prior to baseline) and present persistent/stable symptoms (ADHD-RS ≥ 28). Participants will be divided into two equally sized groups (n = 52) that will either receive Sincrolab Adults or be placed in the control group.

The Sincrolab’s medical device consists of 14 tasks/games distributed across training sessions. Each training session includes a predetermined number of tasks, ensuring that different tasks are trained on each day. Each of the 14 tasks/games has a series of parameters that define them and allow for the identification of the cognitive processes involved (e.g., number of stimuli, number of distractors, stimulus speed, inter-stimulus interval, etc.). The intervention supports (a) the integration of various cognitive processes within each rehabilitation task/game; and (b) the adaptation of difficulty levels across the 14 tasks/games that make up the tool, based on each user’s performance in previous training sessions. The algorithms within the patented AiSA© artificial intelligence system adjust the difficulty level of cognitive stimulation tasks. Once AiSA has data on the participant’s performance during the initial cognitive training sessions, it uses this information to personalize the difficulty level of the tasks for each session and participant. In this way, cognitive training is completely personalized to each user.

The sample size per group in a two-sample design was calculated based on previous results [32] and using a moderate effect size (d = 0.62), as this provides a measure of the treatment effect. The required sample size will also assume a 20% dropout rate, resulting in 104 total participants, 52 per group.

The formula for the sample size per group in a two-sample design from Cohen (1988) [38] is used:n = 2⋅(z_α/2_ + zβ)^2^/d^2^
where:z_α/2_: Critical value for the significance level (α = 0.05) = 1.96.zβ: Critical value for power (1 − β = 0.801) = 0.84.d: Effect size (d = 0.62).n: Sample size per group.

The study protocol (Figure 1) will span 12 weeks plus an additional month of follow-up, with three assessments (baseline, post-intervention, and follow-up). Participants in the intervention group will use a digital cognitive training program designed to target multiple cognitive functions associated with ADHD dysfunctions. The program will include adaptive training games that can be played on a computer or mobile device. Participants will play the training games 3 to 5 times per week, for 15 min per session, over a 12-week period. Participants in the control group will not receive the intervention during the 12-week trial but will be offered access to the program after the study concludes.

The study flow diagram is as follows:

Inclusion criteria.

Participants must meet all of the following:○Adults aged 18 and older○Clinical diagnosis of ADHD according to DSM-5 criteria, confirmed using the DIVA 5.0 Interview for Attention-Deficit/Hyperactivity Disorders Studies (Adult version)○Stable use or non-use of ADHD medications for at least 2 weeks prior to enrollment and throughout the 12-week study period○Baseline ADHD-RS score ≥ 28○Ability to understand and follow written and verbal instructions in Spanish, as assessed by the Principal Investigator or study coordinator○Completion of the informed consent form○Access to a compatible digital device○Willingness and ability to comply with all study procedures and testing requirements

Exclusion criteria.

Participants meeting any of the following will be excluded:○Co-occurring neurological disorders or severe psychiatric conditions (e.g., schizophrenia, bipolar disorder)○Suicidality, as assessed using the Columbia-Suicide Severity Rating Scale (C-SSRS)○Motor impairments (e.g., physical deformities of the hands/arms) preventing gameplay, as reported by the participant or observed by the investigator○History of moderate or severe substance use disorder within the 12 months prior to informed consent○History of seizures (excluding febrile seizures), significant tics, or current diagnosis of Tourette’s Disorder○Known sensitivity to video games (e.g., photosensitive epilepsy, lightheadedness, dizziness, nausea, or motion sickness)○Any medical condition that, in the opinion of the investigator, may confound study data or assessments○Planned initiation of or significant changes in non-pharmacological behavioral therapy during the study○Planned initiation of or significant changes in non-pharmacological training (e.g., game/app-based cognitive training or neurofeedback) during the study

### 3.2. Withdrawal

Participants who choose to withdraw from the study for reasons not defined in the research protocol may do so without needing to justify their decision. However, the potential causes for withdrawal are anticipated to include the following: (1) Inability to comply with the training protocol due to scheduling conflicts, (2) the occurrence of an adverse event in the participant’s family, and/or (3) the occurrence of adverse events affecting the participant.

When a participant notifies their intention to withdraw from the study, a follow-up call will be made to encourage compliance. If this is not possible, an attempt will be made to obtain feedback regarding the reason for their withdrawal from the study.

### 3.3. Treatment Allocation

Participants will be randomly assigned to treatment groups (experimental vs. control). Both groups will undergo the same evaluations: CPT, ADHD symptoms, and Quality of Life questionnaires. This will be a single-blind study. The evaluators (assessors and data analysts) will remain blind to the experimental condition of the participants, which will only be revealed after the final visit. At that point, control group participants will have the option to receive the treatment with the same duration of intervention as the experimental group.

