It is also important to consider that observed improvements on performance-based tasks may be influenced by practice effects, and changes in self-reported outcomes could partly reflect expectancy biases, especially given the use of a treatment-as-usual control rather than an active placebo. While outcome assessors and data analysts are blinded to group allocation to reduce detection and analysis bias, participants are aware of their assignment, which may affect subjective reporting. These limitations will be carefully considered when interpreting the findings and will be addressed through sensitivity analyses where appropriate.

Additionally, this trial will explore potential moderators such as ADHD subtype (inattentive vs. combined), medication status, adherence to training, and use intensity. These variables may help identify individuals most likely to benefit from cognitive training. The inclusion of a 1-month follow-up will also provide preliminary insight into the durability of treatment effects, which remains a critical issue in digital health interventions.

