### 4.1. Strengths

One of the primary strengths of this study is its personalized, adaptive treatment approach. Sincrolab Adults utilizes a series of adaptive cognitive training games that dynamically adjust to match each participant’s individual cognitive profile. This level of personalization is expected to enhance engagement and treatment adherence, potentially leading to greater efficacy than conventional, non-adaptive interventions.

A key strength of this study is the single-blind design, in which both outcome assessors and data analysts are blinded. This approach minimizes detection and analysis bias, enhancing the reliability and validity of objective cognitive and functional outcomes. Although patients are aware of their group assignment and placebo or performance effects cannot be fully controlled, the design ensures robust assessment of treatment effects while maintaining internal validity. Additionally, the research team, including Sincrolab, has extensive experience in digital therapeutics (DTx) research and ADHD clinical studies, ensuring high methodological rigor in recruitment, treatment delivery, data collection, and analysis. The expertise of the investigators and the established research infrastructure contribute to the feasibility and successful execution of this trial.

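### The data analysts' blind is stated to end at the final visit and is not tied to database lock or the finished analysis, so the claimed protection from analysis bias is not secured as written

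*Protocol article*

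**What the plan says.** Section 3.3 (Treatment Allocation) sets a single end to the blind for two groups of people. It says that the evaluators, by which it means both assessors and data analysts, "will remain blind to the experimental condition of the participants, which will only be revealed after the final visit". The sentence that follows attaches another event to the same moment: "At that point, control group participants will have the option to receive the treatment with the same duration of intervention as the experimental group".

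The article then relies on analyst blinding twice. The Discussion (section 4) says that "outcome assessors and data analysts are blinded to group allocation to reduce detection and analysis bias". Section 4.1 goes further: "A key strength of this study is the single-blind design, in which both outcome assessors and data analysts are blinded", and it adds, "This approach minimizes detection and analysis bias, enhancing the reliability and validity of objective cognitive and functional outcomes".

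Section 3.1 (Design and Participants) describes the single blind more narrowly: "Outcome assessors will be blinded to group allocation". Section 4.2 likewise names only outcome assessors.

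**The concern.** Blinding assessors and blinding analysts guard against different things. An assessor who knows the arm may administer or score a test differently, and that risk ends with the last assessment. An analyst who knows the arm may clean, impute or model the data differently. That risk lies mainly in the period after the data are collected and before the results are fixed.

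Section 3.3 gives both groups the assessors' end point. If the codes reach the analysts at that moment, they are masked while the data come in and unmasked when they take their decisions on the complete dataset. The article would then be claiming a safeguard against analysis bias for a period that its own rule does not cover. This matters more because section 4.1 presents the blinding as a key strength, says that the research team includes Sincrolab, and refers to that team's role in the analysis.

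**Working it through.** The point rests on no figure, so the check sets the sections side by side.

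1. **When the blind ends.** Only section 3.3 says, and the event it names is the final visit. It mentions neither database lock nor completion of the analysis.

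2. **Which visit that is.** Section 3.1 lists three assessments: baseline, post-intervention and follow-up. The last falls one month after the 12-week period, so the final visit is a follow-up visit. The article does not say whether it is each participant's own last visit or the last one in the trial.

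3. **What analysis must come later.** Section 3.5 assesses durability by adding time points to the mixed-effects models. That needs follow-up data. Cleaning those data, imputing missing follow-up values, choosing among those models by BIC, checking residuals and fitting the final versions cannot be finished before the last follow-up visit.

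4. **What could come earlier.** The primary comparison runs from baseline to post-intervention (section 3.6). It could in principle be completed while follow-up is still under way, with analysts masked. The article does not say that it will be.

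5. **Match between claim and rule.**

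| Group | Bias at issue | Period that needs masking | Covered by the stated end point? |
|---|---|---|---|
| Assessors | Detection | Up to the last assessment | Yes, if the final visit is the last in the trial |
| Data analysts | Analysis | Until dataset, imputation and model are final | Not secured |

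6. **Effect on the design figures.** The stated sample size reproduces: n = 2 × (1.96 + 0.84)² / 0.62² = 15.68 / 0.3844 = 40.8, so 41 per group. Allowing for 20% dropout, 41 / 0.80 = 51.25, so 52 per group and 104 in total, as stated. The timing of unblinding enters none of these quantities.

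**The case against.** The best defence is that section 3.3 sets an earliest time for the reveal and not a date on which analysts receive the codes. The offer to controls concerns access to the program, not the release of a code list. Sections 4 and 4.1 put no time limit on analyst blinding, so the intention may well be that analysts stay masked throughout. Code-break procedures are also often left to a full protocol or SAP. The first part stands: a reveal after the analysis is not excluded. The last part does not fully answer the point, because the article does state an end to the blind and does claim a benefit that this end point fails to secure.

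Several stronger readings are tempting, and the documents do not support them:

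- **That analysts are certainly unmasked before the analysis, or that their blinding is absent.** No analysis date is given, and analysts are stated to be blind up to the final visit.
- **That allocation is revealed participant by participant while others are still being assessed.** The undefined term permits this reading, but section 3.1 offers controls access once the study has concluded, which favours the end-of-trial reading.
- **That training logs would unmask the analysts.** Section 4.2 says that adherence is monitored, not who sees the records.
- **That section 3.5 leaves the treatment comparison wide open.** Multiple imputation is specified, with complete cases as a sensitivity comparison. The choice of correlation coefficient concerns only exploratory associations. The primary outcome, main fixed effects and random intercept are stated. BIC selection is the clearest remaining data-dependent step, and BIC does not reward a favourable treatment p-value.
- **That a type I error inflation can be attached.** The documents give neither the number of candidate analyses nor their correlation. Masked codes would not stop someone choosing the smallest two-sided p-value; pre-specification does that.

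**Conclusion.** The concern holds in a limited form. The only stated end of the analysts' blind is the final visit, and work that analyst blinding is meant to protect comes after it. The reduction in analysis bias claimed in sections 4 and 4.1 is therefore not secured by the text. It may still be achieved in practice if the codes are held back longer than the article says.

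The conclusion rests on two readings: that the final visit is a follow-up visit, which the schedule in section 3.1 supports, and that the reveal at that point extends to the analysts, which is the natural reading of section 3.3 but is not spelled out. No numerical size can be given. The point is worth correcting because the article presents this blinding as a key strength and the correction is nearly free.

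**What to change.** In section 3.3:

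- Define the final visit as the last participant's follow-up visit, and keep assessors blind until then.
- Separate the release of allocation to participants and to the staff who offer delayed access from its release to analysts. Sections 4 and 4.1 say that participants already know their arm, so offering controls the program does not require the analysts to be told anything.
- State that analysts work with group codes A and B until the database is locked and the primary dataset, the imputation and the primary model are final.

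If the sponsor does not want to commit to this, the analysis-bias claim in sections 4 and 4.1 should be withdrawn.

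The cost is a few sentences and an allocation file held by someone outside the analysis. Sample size, alpha and power do not change.
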